**Fig. 2 Fig2:**
[figure not shown]
Example of an instruction screen in TAS Test for a finger tapping task [38]. The video instructions are on the left, the text instructions on the right, with the audio icon underneath (so participants can listen to the instructions if preferred). When the participant is ready to attempt the task, they press the ‘Next’ button to move on to the ‘recording’ screen. The green circles above the written instructions show the participant their progress through the various tasks

On each instruction screen, participants will be shown a 5–10 s looped video that demonstrates the hand, or speech-like movement that is required for the task. There are text instructions next to the video and participants may click on an ‘audio’ icon if they would like to hear spoken instructions (the text instructions are read out aloud). When participants are performing the hand or speech-like movements on the ‘recording’ screen, the computer video camera will record the hand movement data and the computer microphone will record the audio data respectively.

### Hand movement data collection

For each of the hand movement tests, the participant is asked to hold their hands up about 50 cm in front of the computer camera and adjust their position until they can see an image of their hands on the screen fitting completely inside green ‘data collection’ boxes. This careful positioning of the hands at the start of each test assures that the camera can record the movement patterns accurately. Computer-user interface technologies are embedded into the TAS Test software that respond to the positioning of the participant’s hands and give them on screen text prompts (e.g., “your right hand is correctly positioned”, “move your left hand closer to the screen”, or “well done your hands are in the correct position”) to prompt adjustments in the hand positioning as required. These technologies have been purposefully included to allow TAS Test to collect robust data at home, or any remote setting, without any in-person researcher assistance being required [42].

The hand movement tests comprise tests of repetitive finger tapping (index finger tapping against thumb) tests, and of repetitive ‘sequential’ finger tapping (index, middle then ring finger each in turn tapping against the thumb, then index, middle, ring etc.). The sequential finger tapping tests are a commonly used clinical test of motor function chosen in this study for direct comparison with the Sequential Motion Rate analysis in the DDK test. Each test is about 10 s duration and completed in a fixed order as follows: (i) at a comfortable pace: right hand finger tapping, left hand finger tapping, right hand sequential finger tapping, left hand sequential finger tapping; (ii) at a maximal pace ‘as big and fast as you can’: right hand finger tapping, left hand finger tapping, right hand sequential finger tapping, left hand sequential finger tapping; (iii) at maximal pace: both hands finger tapping together in phase, both hands finger tapping together out of phase, both hands finger tapping together in phase with a cognitive task, both hands finger tapping together out of phase with a cognitive task.

‘In phase’ means that both hands move simultaneously through the finger tapping cycle, whereas ‘out of phase’ means that each hand moves through the finger tapping cycle in the opposite direction to the other hand (i.e., 180 degrees out of phase so one hand has the finger and thumb opposed while the other hand has the finger and thumb spread apart). The cognitive task will be counting backwards aloud from 100 and constitutes a ‘dual motor-cognitive test’ when performed at the same time as finger tapping [53, 54]. Each hand will therefore be tested separately, and together, at a comfortable pace and at maximal pace, allowing for a number of finger-tapping measures to be calculated including, but not limited to, frequency, rhythm, inaccuracies (i.e. the wrong digit tapped on the sequential tests), ‘motor reserve’, calculated as a ratio (the maximal pace parameter divided by comfortable pace parameters), bimanual ‘motor cost’, calculated as the finger tapping parameters of one hand divided by the finger tapping parameters of same hand when both hands tapped together and the ‘dual cognitive-motor cost’, calculated as the finger tapping parameters divided by the finger tapping parameters during the counting backwards aloud from 100 task.

We will shorten this finger tapping protocol to around three to five tasks, aiming for a test duration of 2 to 3 min, in the smartphone version of TapTalk that will be used in Aim 2 and Aim 3. The choice of which tasks will comprise the shortened protocol will be based on the findings from Aim 1. We have purposefully kept a wide array of tests in Study 1 to clarify which tests combine best together, and with the DDK data, to best discriminate biomarker-defined AD pathology.

### Speech-like data collection

It is unclear which tests are most sensitive in preclinical AD. We will replicate the clinical DDK [23, 27] test but under both comfortable and maximal speed conditions. A participant will be instructed to say “pa, p.a., pa…” repetitively for 10 s at a comfortable pace, then the participant will be instructed similarly for “ta, ta, ta…”, “ka, ka, ka…” and “pa-ta-ka, pa-ta-ka…” all at a comfortable pace. After this, they will be instructed, to repeat each test in turn but this time at maximal pace. These deceptively simple tests assess the motor function of the lips (p.a.), tongue (ta) and palate (ka) respectively, allowing us to calculate the speed, rhythm, accuracy, and motor reserve (‘maximal pace’ measures divided by ‘comfortable pace’ measures) for each syllable.

Similar to the format of the hand movement tests, there will be an ‘instruction’ screen and a ‘recording’ screen followed by a “well done” screen. The difference compared to the hand movement tests, in terms of the software, is that the recording screen does not show a video image of the participant as they perform the task; see Fig. 3. At the end of the protocol, the participant will be asked to complete a questionnaire on their experience of the tests and suggestions for improvement.

**Fig. 3 Fig3:**
[figure not shown]
Speech-like test protocol: (**A**) a ‘get ready’ screen appears for 5 s immediately after the instruction screen (not shown); (**B**) the recording screen includes brief prompts such as “pa” and a visual count down for 10 s to encourage participants to keep repeating the speech-like sounds for the full period of recording

### Extracting hand-speech movement data

We will use deep neural networks and other machine learning methods to develop and train two computer programs that will automatically detect, respectively, hand key points (e.g. finger and thumb tips) in the video data [43], and syllable features in audio recording (Fig. 1). A series of movement features will be extracted in a fixed window period, by (1) experts in hand movement (JA, KL, [name]) and speech-like movements (LG), and (2) deep-learning approach applied directly on processed video data, to analyse their associations with biomarker-defined measures of AD pathology. The processed video data can be the hand-only cropped video or displacement (between fingertip and thumb-tip) over time data extracted from the raw video. Thus, two approaches, expert guided and AI-based ‘deep-learning’, will extract discriminative hand-speech movement features as input data for the multivariable model. The main outcome will be a validated personal computer (laptop and desktop) version of the TapTalk that discriminates preclinical AD from normal ageing in cognitively healthy adults ≥ 50 years old with defined sensitivity and specificity.

### Statistical analysis

We will use data from 350 of a sample of 500 participants to develop multivariable models that classify data according to risk of preclinical AD pathology. Data from the remaining 150 will determine the externally validated sensitivity/specificity of candidate models in detecting preclinical AD. Hand-speech movement data will be normalised. Participants with blood biomarker levels in the preclinical AD range (e.g., p-tau 181, or a combination of blood biomarkers) will be classified as ‘AD positive’. We will use penalised logistic regression to measure the associations between movement patterns and AD positivity. Covariates may include age, gender, apolipoprotein E ([APOE] a risk gene for AD analysed through blood sampling as part of the ISLAND Project), years of education, and handedness. As a secondary, more agnostic approach, we will use deep learning methods to discover features in movement and speech-like data that map to AD positivity.

We will use cross-validation to avoid overfitting by selecting penalty terms (type and amount of shrinkage applied to coefficients) which optimise the bias-variance trade-off. Bootstrap procedures will be used to estimate model uncertainty. We will externally validate models using data from the remaining 150 participants. Receiver Operating Characteristic (ROC) curves will be plotted against the positive AD cut-off to assess the sensitivity/specificity of movement and speech-like models to discriminate the preclinical AD stage from normal ageing. The model with the highest area under the ROC curve (AUC) will be chosen as the TapTalk algorithm.

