#### Design

We will undertake a cross-sectional single site study. Overview of the methods is presented in Fig. 1.

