#### Participants

We aimed to recruit at least 500 eligible participants (see below for inclusion and exclusion criteria) with normal cognition from the ISLAND Project. As of March 2024, we have recruited 1382 adults, with mean (SD) age 66.20 (7.65) years, range 50–92 years, and 72.07% female. The ISLAND project was launched in October 2019 at the University of Tasmania as a 10-year prospective cohort study of Tasmanians ≥ 50 years old with nested interventions to reduce dementia risk [45, 46]. To date, > 14,000 people have been recruited to the ISLAND Project; 8,500 research participants (mean age 63 years) have provided detailed demographic and health data, 3,000 have completed the online validated Cambridge Neuropsychological Test Automated Battery (CANTAB) cognitive tests [47], 1,800 have completed online motor-cognitive tests (TAS Test) [38] and more than 1,500 have provided blood samples. Paired Associates Learning (PAL) scores distinguish between older adults with MCI and those who are cognitively healthy with a sensitivity/specificity of 0.83/0.82 [48]. The online ISLAND Project surveys are repeated annually with cognitive performance and blood-based biomarkers collected every second year.

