##### Inclusion criteria

Adults ≥ 50 years old who are (i) participants in the ISLAND Project [45] (ii) have provided a blood sample for analysis of blood-based biomarkers, (iii) have *normal* cognition defined as not ≥ 2 SD above the mean total errors (adjusted for age) on the CANTAB PAL tests, and (iv) have no history of persistent cognitive symptoms reported on ISLAND Project questionnaires (all participants are asked each year: *Have you noticed a substantial change in your memory and mental function in recent years*? [YES/NO], *Have you been told by a doctor that you have dementia?* [YES/NO], *Have you been told by your doctor that you have a memory impairment but they were uncertain if you have dementia?* [YES/NO], *Have you discussed concerns about your memory and mental function with your doctor or other health professional?* [YES/NO]).

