### Sample size justification

The precise combination of blood-based biomarkers used to determine ‘positive’ preclinical AD pathology is yet to be determined as the scientific literature is developing quickly and new biomarkers are being developed regularly. We will review the literature before deciding on the best biomarker test, or combination of tests, that should be used to define AD pathology risk most accurately.

Currently p-tau 181 is considered one of the most accurate blood-based biomarkers for preclinical AD risk and we have therefore based our sample size calculation on this biomarker. As new tests are developed and are likely to be even more sensitive/specific than p-tau 181, the current calculation is a conservative estimate. We estimate that 17% of cognitively normal adults within our cohort have p-tau 181 in the preclinical AD range [55]. There are no tests of DDK compared to AD biomarkers, so we have based all calculations on finger tapping data.

We have performed ROC curve analysis using open data from Mollica et al. to calculate sensitivity and specificity of finger tapping speed and variability to predict CSF p-tau 181 [20]. This showed area under ROC curve (AUC) of 0.75 for a null linear model including age, gender and years of education, but not finger tapping. We calculated that the sample size to compare a screening test with an AUC > 0.90 against the null model requires 60 preclinical AD cases (positive p-tau181) and 290 healthy ageing controls (negative p-tau181). Thus, we will use 350 in the development dataset (expected 60 [17%] preclinical AD cases) and 150 in the validation dataset (expected 25 [17%] preclinical AD cases) to test cut-offs from the development model. The PROBAST tool [56] for assessment of prediction and diagnostic method studies confirms these development and validation strategies have a low risk of bias.

### AIM 2

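### Aim 1 calls accuracy in the held-out 150 externally validated, but they are the rest of one single-site ISLAND sample, so this is internal validation

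*Protocol article*

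**What the plan says.** All references are to the protocol article.

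- Aim 1, Design: "We will undertake a cross-sectional single site study".
- Aim 1, Participants: the recruitment target is at least 500 people "with normal cognition from the ISLAND Project". The same section adds: "As of March 2024, we have recruited 1382 adults". Membership of ISLAND is also the first inclusion criterion.
- Aim 1, Statistical analysis: "We will use data from 350 of a sample of 500 participants to develop multivariable models". On the rest it says: "Data from the remaining 150 will determine the externally validated sensitivity/specificity of candidate models in detecting preclinical AD". The next paragraph repeats this: "We will externally validate models using data from the remaining 150 participants".
- Aim 1, Sample size justification: the second part is "150 in the validation dataset (expected 25 [17%] preclinical AD cases) to test cut-offs from the development model". Here it is called a validation dataset, without the adverb.
- Extracting hand-speech movement data: the main outcome of Aim 1 is a validated computer version of the test with defined sensitivity and specificity.

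**The concern.** External validation means testing a finished model on people drawn from somewhere other than the development data, such as another population, place, period or laboratory. Its purpose is to show whether accuracy travels. A held-out part of one sample answers a narrower question: whether the model has fitted noise in the development part.

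The two Aim 1 sentences claim the first property for a design that has only the second. The hold-out is also the only planned accuracy test of the classifier against the blood biomarker. A reader who takes the label at face value would treat the reported sensitivity and specificity as evidence of transportability, which the study will not have collected.

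The article uses the same term differently later. In the Aim 3 sample size section it describes the result of Study 3, which recruits separately from a hospital and a cognitive clinic. One term for a split sample and for a separately recruited cohort invites misreading.

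**Working it through.** **1. The split itself.** Inputs from the Aim 1 Statistical analysis and Sample size sections: 350, 150, and a planning prevalence of 17%.

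- 350 + 150 = 500, the whole sample.
- 0.17 × 350 = 59.5 (stated 60), and 0.17 × 150 = 25.5 (stated 25).
- 60 cases + 290 controls = 350.

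The figures reproduce. The problem is the name given to the split, not its arithmetic.

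**2. Where the two parts come from.**

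| | 350 | 150 |
|---|---|---|
| Sample | part of one sample of 500 | the remainder of that sample |
| Source cohort | ISLAND Project | ISLAND Project |
| Study site | single site | single site |
| Eligibility | Aim 1 criteria | Aim 1 criteria |

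Aim 1 names no second cohort, site, period or laboratory for the 150. The recruits beyond 500 (1,382 − 500 = 882) do not supply one either, because recruitment for Aim 1 is from ISLAND.

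**3. Whether a later study supplies the missing test.** Such a study would have to test the classifier against the blood biomarker, in asymptomatic people, outside ISLAND.

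- Study 2.1 compares recording devices, and Study 2.2 measures usability and reliability in people who took part in Study 1. Neither tests diagnostic accuracy.
- Study 2.3 uses ISLAND participants and classifies them as stable or declining on CANTAB. It has the same cohort and a different reference standard.
- Aim 3 recruits at a hospital and a clinic, but the people have cognitive symptoms and the reference standard is consensus clinical diagnosis.

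None meets all three conditions.

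**4. What an interval from the hold-out would cover.** As an illustration, assume observed sensitivity and specificity of 0.80, with 25 cases and 150 − 25 = 125 controls. The exact (Clopper-Pearson) 95% intervals are:

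- sensitivity 20/25 = 0.80: 0.59 to 0.93
- specificity 100/125 = 0.80: 0.72 to 0.87

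These describe sampling error within this cohort. They contain no component for a change of population, site or laboratory, and nothing in the design allows one to be estimated.

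**The case against.** The strongest reply is that the article hides nothing. It says that the 150 are what is left of the 500 and that the study has a single site. The adverb may be meant only to separate held-out data from the cross-validation and bootstrap described alongside it. No estimate, cut-off or sample size changes if the word changes. The claims of wide use in the Discussion are conditional on the test proving valid, and they concern the smartphone app, which has further studies. All of that is fair, and it limits the remedy to wording. It does not make the word correct: the term has an established meaning, and it is attached to the central accuracy result of Aim 1.

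A second reply is that the article does not say how the 350 and 150 are chosen, so the split could follow recruitment date or region. That is possible, and a random split should not be assumed. Such a split would still lie within one cohort and should carry its own name.

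A reader might infer more than the documents support:

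- *The two parts share one software version and one label rule, with no variation between participants.* The article says that the TAS Test software will be adapted and leaves the biomarker rule open. It also allows testing at home, elsewhere or at a university site, on different computers. Nothing ties that variation to one part of the split, so it does not make the 150 external, but it rules out an absolute statement.
- *The common 17% shows identical case mix.* It is one planning prevalence applied twice, and it could equally have been applied to a separate cohort.
- *The 1,382 recruits should be re-allocated by date or region.* The article gives neither their recruitment dates and regions nor the number who are eligible with usable biomarker results. Such a split would also stay within one cohort.

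**Conclusion.** The concern holds as a misstatement of what the design delivers. Both sentences in the Aim 1 Statistical analysis claim external validation, while the design gives held-out internal validation. This would be so even for a single model locked in advance, so the point is separate from how the winning model is chosen.

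No numerical size can be given. The split is internally consistent, and the documents give no basis for predicting how far accuracy would change elsewhere. In particular, they do not show that it would fall. The consequence lies in interpretation: Aim 1 can support a statement about accuracy in ISLAND volunteers, but not about transport beyond them. The conclusion rests on the article as shown, in which no second source for the 150 is described.

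**What to change.** In both sentences of the Aim 1 Statistical analysis, replace *externally validated* and *externally validate* with *internally validated (held-out sample)* and *internally validate (held-out sample)*. Add one sentence saying that external validation of the classifier against the blood biomarker remains outstanding, because Study 2.3 and Aim 3 use other reference standards. If the 150 are in fact selected by recruitment date or region, say so and call it temporal or geographic validation within one cohort.

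The cost is a few words. No new data, re-allocation of participants or change to the sample size is needed.

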### Sample size justification

Using CANTAB cognitive test responses already collected in the ISLAND Project (n = 3,000), we estimate that we will collect > 1,000 complete cases (TapTalk app completion twice in 18 months and CANTAB at baseline and 24 months), which is ample for logistic regression with a single fixed-effect predictor variable.

### AIM 3

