### Statistical analysis

We will calculate AUC for TapTalk and MoCA (or RUDAS) to predict clinical diagnosis of MCI and AD dementia (defined as AD or mixed AD/vascular); 95% confidence intervals will be obtained using bootstrapping. Covariates may include age, gender, APOE4, years of education, and handedness. We will estimate cut-off scores for TapTalk and MoCA (or RUDAS) to differentiate between cognitively unimpaired vs. MCI, and between cognitively unimpaired vs. AD using the Youden index to optimise the trade-off between sensitivity and specificity. Classification accuracy (sensitivity and specificity) using these cut-offs will be compared using McNemar’s test. Participants diagnosed with other types of dementia (such as Dementia with Lewy Bodies or Frontotemporal Dementia) will not be included in this analysis.

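### Aim 1 is sized against a demographic null model, but its analysis selects on highest raw AUC and makes no comparison with a covariate-only model

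*Protocol article*

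**What the plan says.** The hypothesis (Protocol article, Aims and hypothesis) is that patterns of hand and speech movement detect risk of AD pathology.

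The Aim 1 Statistical analysis section relates movement data to biomarker positivity by penalised logistic regression. It continues: "Covariates may include age, gender, apolipoprotein E ([APOE] a risk gene for AD analysed through blood sampling", with years of education and handedness also listed. Candidate models are developed on 350 people and assessed on 150, and then: "The model with the highest area under the ROC curve (AUC) will be chosen as the TapTalk algorithm". The section names no comparator and no minimum gain.

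The Aim 1 Sample size justification has a different question in view. It reports an AUC "of 0.75 for a null linear model including age, gender and years of education, but not finger tapping", and states that "the sample size to compare a screening test with an AUC > 0.90 against the null model requires 60 preclinical AD cases" and "290 healthy ageing controls (negative p-tau181". It then gives the 150-person validation set the task of testing cut-offs.

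The Background describes TapTalk as non-invasive, and the closing summary of the Discussion lists low cost, accessibility and non-invasiveness as its advantages.

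**The concern.** The two sections answer different questions. The sizing asks whether a test with movement data discriminates better than demographics. The analysis asks only which candidate has the largest AUC. When covariates are allowed and the rule is highest AUC, anything that raises the AUC is favoured, whether it is movement, age or a genotype. The resulting AUC, sensitivity and specificity describe the whole model and cannot be credited to movement, which is what the hypothesis is about.

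APOE raises a second problem. It comes from a blood sample, so an algorithm that uses it as an input is no longer the phone-only, non-invasive test that the article describes. The null model used for sizing contains neither APOE nor handedness, so even a gain over that null model could come from those two variables.

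**Working it through.** **Inputs.** From the Aim 1 Sample size justification: null AUC 0.75; alternative AUC 0.90; 60 cases and 290 controls for development; about 25 cases among 150 for validation; prevalence 17% (0.17 × 350 = 59.5; 0.17 × 150 = 25.5). Alpha, sidedness, power and the correlation r between the two AUCs are not stated. I assume two-sided 5% and r from 0 to 0.5 unless noted.

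**Formulas.** Hanley–McNeil variance for AUC A with m cases and n controls:

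V = [A(1−A) + (m−1)(A/(2−A) − A²) + (n−1)(2A²/(1+A) − A²)] / (mn).

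For two AUCs on the same people, Var(diff) = V₁ + V₂ − 2r√(V₁V₂), and power = Φ(0.15/SE(diff) − 1.96).

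**Step 1: the plan's own figure.** With 60/290 the standard errors are 0.0384 (A = 0.75) and 0.0272 (A = 0.90). At r = 0, SE(diff) = √(0.0384² + 0.0272²) = 0.0471, and power = Φ(0.15/0.0471 − 1.96) = 89%. It is 97% at r = 0.3 and 99% at r = 0.5. Working back to the number of cases, all at r = 0:

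| Alpha | Power | Variance used for the test | Cases |
|---|---|---|---|
| one-sided 5% | 90% | null (both AUCs 0.75) | 60 |
| two-sided 5% | 80% | null (both AUCs 0.75) | 57 |
| two-sided 5% | 90% | unpooled | 63 |

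The figure is therefore consistent with a comparison of 0.90 with 0.75. It cannot be confirmed exactly, because the settings are not given.

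**Step 2: the same comparison in the hold-out set.** With 25/125:

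- A = 0.75: V = (0.1875 + 24 × 0.0375 + 124 × 0.0804)/3125 = 0.00354, SE 0.0595.
- A = 0.90: V = (0.09 + 24 × 0.00818 + 124 × 0.0426)/3125 = 0.00178, SE 0.0422.
- r = 0: SE(diff) = 0.0729, power = Φ(2.06 − 1.96) = 54%.
- r = 0.3: power 68%. r = 0.5: power 81%.

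If the true full-model AUC is 0.85, power is 25–44%. If it is 0.80, power is 9–14%.

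**Step 3: what a raw AUC can show.** A model whose movement terms add nothing would be expected to have the AUC of its covariates. Taking 0.75 as an illustration, the approximate 95% interval in 25/125 is 0.75 ± 1.96 × 0.0595 = 0.63 to 0.87. A hold-out AUC in the mid-0.80s is thus within chance of a covariate-only model, and the raw figure does not reveal its source.

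**Step 4: the selection rule.** In a simulation with 25/125, each candidate was a demographic score (AUC 0.75) plus pure noise (SD 0.3 or 0.6 of the score's within-group SD). Selection and assessment used the same 150 people. With 5 to 20 candidates, the best one beat the demographic score in 57–99% of runs, with a mean best AUC of 0.75–0.77. This is illustrative only: it does not mimic penalisation, and the article does not say outright in which data set the highest AUC is judged.

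**The case against.** The strongest reply is that the comparison is declared in the sizing paragraph, and that a condensed article may leave its test and data set to another document. The covariates are optional. Movement features are described as the input to the multivariable model (Extracting hand-speech movement data), the regression is meant to measure the association between movement and positivity, the ROC curves are for movement and speech-like models, and the secondary deep-learning approach is described with movement and speech data only. Age or APOE may be meant purely as adjusters.

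Much of this stands. It means the harm is possible, not certain. A reader might infer that TapTalk will carry no movement information, or that the protocol specifies an APOE-dependent algorithm. The text supports neither.

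It does not remove the mismatch. The selection rule is stated here, on raw AUC, and it differs from the comparison that the study was sized for. The section does not say whether covariates are adjusters or algorithm inputs.

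A reader might also infer that a model without movement would show AUC 0.75 in this cohort, and that only the excess over 0.75 counts. That does not follow. The 0.75 was computed for CSF p-tau 181, using open data from a study of about 70 older adults that the Background describes as covering preclinical AD and AD dementia. Aim 1 uses a blood marker in cognitively normal adults, where the demographic AUC is unknown. For a movement-only model, an AUC of 0.75 would itself be evidence.

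Nor does the point extend to Study 2.3 or Aim 3. An unadjusted single-predictor model is legitimate for a score's predictive validity, and Aim 3 already has MoCA or RUDAS as comparator.

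**Conclusion.** The point holds for Aim 1. The sizing comparison and the analysis do not match, and if covariates enter the chosen model, its accuracy could not be attributed to movement on the analysis as written. APOE as an algorithm input would in addition contradict the article's own description of the test.

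The share of accuracy that covariates might supply in this cohort cannot be derived from the document; 0.75 is an illustration only. The power figures rest on the Hanley–McNeil variance and on an assumed alpha and correlation. Nothing here shows the 60/290 figure to be wrong.

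**What to change.** In the Aim 1 Statistical analysis section, state whether covariates are adjusters or algorithm inputs, and add:

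- **(a)** The AUC of a movement-only model will be reported.
- **(b)** For any model with covariates, the paired AUC difference from a model with exactly the same covariates and no movement features will be reported, with a bootstrap or DeLong 95% CI, in data not used for selection. In practice the algorithm is chosen by cross-validation within the development set, and the hold-out set is used once.
- **(c)** APOE will not be an input to the deployed TapTalk algorithm and will appear only in a sensitivity model.

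**Cost.** No new variables are needed, since the plan already names all the covariates. The headline may shrink from a total AUC to an added AUC. At 25/125 the hold-out comparison has only about 54–81% power even for 0.90 versus 0.75, so it should be presented as an estimate with its CI and not as a pass/fail test.

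A larger hold-out set would help. At the plan's 60:290 ratio (two-sided 5%, unpooled variance), 80% power needs 47 cases at r = 0 (47 × 350/60 ≈ 274 people) or 25 at r = 0.5 (≈ 146 people). The 1382 people already recruited might allow this, but the article does not say how many of them are eligible and have biomarker results.
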